### Weight and length growth trajectories between birth and 12 months

A linear mixed-effects regression model with an unstructured covariance matrix will be used to examine the effect of the intervention on weight and length velocity from birth to 6 months and 6 to 12 months [74]. The effect of intervention on secondary outcomes will be assessed using the same methods as for the primary outcomes.

### Pre-specified sub-group analysis

Sub-group analyses will be conducted by maternal height (< 150 cm and ≥ 150 cm), underweight (MUAC < 23 cm and BMI < 18.5 kg/m^2^), years of education (< 12 and ≥ 12 years), and the wealth quintile of the household (defined both using an asset index and total household expenditures). Relative measures of effect within each of these sub-groups will be estimated. An a priori analysis will also be done for types of preterm, i.e., very (gestational age 28–32 weeks) and moderate, i.e., (gestational age 32–34 weeks) preterm.

The method for the generation of the asset index will be similar to the method used by the Demographic and Health Survey Programme (DHS Program) [75]. Gross total household expenditures will be calculated. The latter indicator of socioeconomic position will be used for concentration curves, concentration index (with 95% CI) and differences in the concentration index (with 95% CI) using the *F*-test to explore, summarize, and draw inferences on the equity impact of the intervention package. Additionally, absolute and relative inequalities in ponderal and linear growth of preterm and term SGA infants at 12 months using the slope index of inequality (SII) and relative index of inequality (RII), respectively, will be estimated. Outcomes having higher inequity in the descriptive analysis will be explored further. Stata (StataCorp LLC, College Station, Texas) and standard user-written packages will be used for all analyses [76–79]. The SPIRIT (Standard Protocol Items: Recommendations for Interventional Trials) reporting guidelines were utilized in preparing the methodology of this study (see Additional file 6, SPIRIT checklist) [80].

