### Outcome measures {12}

The primary outcomes include attained weight, and weight for age *Z* scores at 12 months of age.

The secondary outcomes along with timing of their measurements are listed in Additional file 4. The key secondary outcomes for children are proportion stunted, wasted, and underweight at 6 and 12 months; overweight or obesity at 12 months; weight and length velocities between birth to 6 months and 6 to 12 months; neurodevelopment (composite cognitive, language, motor, socio-emotional, temperament and HOME scores; Mean Global Scale for Early Development score) at 12 months [62]; morbidity and hospitalization from birth to 12 months; and dietary assessment, micronutrients, and anemia status at 12 months (in a sub-sample).

The key secondary outcomes for mothers (Additional file 5) are depressive symptoms, nutritional status during the postpartum period, and household consumption and expenditures at 6 and 12 months of infant age, as well as dietary assessment at 3 and 6 months (in a sub-sample).

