### Intervention delivery

The PSE team informs the intervention delivery team about the infants randomized to the intervention arm. The intervention delivery teams conduct the first visit within 24 h of enrolment.

The intervention delivery visits are designed to accommodate the implementation of various components of intervention such as health, nutrition, and psychosocial in a single visit. On a particular visit, the focus is either on nutrition and health of the infant and mother or early child stimulation and responsive care and psychosocial care and support of the mother, with adjustments made as necessary. This intervention includes counselling on early and exclusive breastfeeding, expressing breast milk, kangaroo mother care, responsive feeding, micronutrient supplementation, hand washing, family planning, and immunization. The schedule includes 11 visits (days 1, 3, 7, 10, 11, 14, 17, 21, 22, 24, and 28) in the first 28 days, followed by visits every 2 weeks in months 2 and 3, and monthly visits in months 4, 5, and 6. In addition to providing counselling and support, the team also acknowledges and praises good practices.

During each visit, FAs ask about the well-being of both the infant and the mother. If the infant needs urgent care, the FA informs the supervisor and facilitates referral to the nearest health facility based on the family’s preference. The FA checks the mother’s understanding of the counselling messages and summarizes the key messages at the end of each visit.

If any problem with breastfeeding or complementary feeding is identified, a lactation counsellor or nutritionist intervenes to resolve the problem. If the problem is not resolved, the infants are referred to the pediatrician at the collaborating hospital.

The intervention delivery team FAs are measuring compliance with intervention during their home visits. This is done by both asking questions to the mother and observing empty food supplement packets or counting remaining tablets.

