### Outcome ascertainment {18a}

Infants in both the intervention and control arms are visited at home by an independent outcome ascertainment team in pairs, at infant ages 1, 3, 6, 9, and 12 months, to measure weight, length, and head and mid upper arm circumference (MUAC); assess infant care practices; and document the prevalence of reported illnesses in the previous 2 weeks and care-seeking for illness and hospitalizations since the last visit. Additionally, the team measures the weight and MUAC of mothers at 2, 6, and 12 months postpartum and assesses postpartum depression among mothers using the Edinburgh Postnatal Depression Scale (EPDS), which has been validated for use in India [63].

Weight measurements are obtained using digital weighing scales (Seca model 354; California, USA) with an accuracy of up to 10 g, while infant length measurements are taken using infantometers (Seca model 417; California, USA) with a precision of 0.1 centimeters. Head and MUAC are taken using a measuring tape (model 212; Seca, California, USA) [64–66].

Information on household consumption and expenditures (monthly expenses on food, rent, health care, utilities, maintenance, fuel, reimbursement of loans, and helpers; education and health care expenses in the preceding three months; annual expenses on insurance, and clothes) will be collected at enrollment and 6 and 12 months of age. Neurodevelopmental assessment is done by trained and standardized psychologists. Cognitive, motor, language, and socio-emotional development will be assessed at 12 months of age using the Bayley Scales of Infant and Toddler Development III (BSID-III) [67]. Infant temperament will be assessed at 12 months of age using the Infant Temperament Scale [67, 68]. The child’s home environment will be assessed using the Home Observation of the Environment (HOME) questionnaire (Infant and Toddler version [69]) by the trained field team through physical home visits. Additionally, the Global Scales for Early Development (GSED) scale will be used at 6 and 12 months to assess child development across multiple domains, including cognitive, motor, and social-emotional development. Blood samples (~10 ml) will be collected at 12 months of age for micronutrient assays. The samples will be centrifuged, and serum and blood pellet stored at – 80 °C in the field office. The micronutrient concentrations will be measured in accredited laboratories.

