### Main effects

The primary outcome will be analyzed using an intention-to-treat (ITT) approach. All participants randomized to a treatment group will be included in the analysis, regardless of their adherence to interventions. However, missing data on the primary outcome at 12 months will not be imputed since the key assumption that data will be missing at random would probably not be valid. However, we will use imputation methods depending on the nature of missingness for the secondary outcomes. Some authors might call the above approach modified intention-to-treat analysis; however, there is no clear consensus on the use of this terminology as per the CONSORT guidelines. The statistical precision of the effects will be presented as 95% confidence intervals (Cis). The distributions of WAZ will be presented in Epanechnikov kernel density plots by study arms. To quantify any differences in distribution, the 5th, 10th, 15th, 20th, and… up to the 95th percentiles will be compared using quantile regression. The 95% CI of the difference between the percentile estimates for the two arms will be calculated using bootstrap resampling with 1000 replacements. The percentile differences and corresponding CIs will be visualized in forest plots.

For binary outcomes, we will use generalized linear models (GLMs) of the binomial family with a log-link and an identity-link function to calculate the relative risks and risk differences, respectively. For continuous outcomes, GLMs of the Gaussian family with an identity-link function will be used to calculate the difference in means between the groups.

The effect of the intervention package on infant mortality across both strata will be estimated in a Cox proportional hazards model taking the stratification variable into account. The days of follow-up for each infant will be calculated as the date of enrolment subtracted from the date of the last follow-up or death.

We will adjust for imbalances in baseline features if present.

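### Subgroup effects are fixed on a relative scale that cannot be interpreted for WAZ, and the maternal MUAC/BMI subgroup has no described pre-randomisation measurement

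*Protocol article*

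**What the plan says.** **Effect measure.** *Outcome measures {12}* names two continuous primary outcomes: "The primary outcomes include attained weight, and weight for age *Z* scores at 12 months of age". For continuous outcomes, *Main effects* states: "GLMs of the Gaussian family with an identity-link function will be used to calculate the difference in means between the groups". For binary outcomes it uses log-link and identity-link binomial models "to calculate the relative risks and risk differences, respectively". *Pre-specified sub-group analysis* then sets a different rule for subgroups: "Relative measures of effect within each of these sub-groups will be estimated". That sentence names no outcome and makes no exception.

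**Inequality measures.** The same section plans concentration indices, with an F-test and 95% CI for their differences. It also plans absolute and relative inequality in ponderal and linear growth at 12 months, "using the slope index of inequality (SII) and relative index of inequality (RII), respectively, will be estimated". It does not say whether growth enters as z-scores, as attained weight and length, or as binary deficits.

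**Maternal subgroups.** The section lists maternal height, and underweight defined by MUAC below 23 cm and BMI below 18.5 kg/m². On measurement, *Outcome ascertainment {18a}* says "the team measures the weight and MUAC of mothers at 2, 6, and 12 months postpartum". The baseline information described under *Surveillance, follow-up, screening, and enrollment* names no maternal anthropometry. *Intervention delivery* states: "The intervention delivery teams conduct the first visit within 24 h of enrolment". Mothers in the intervention arm receive daily snacks of 600 kcal and micronutrients for 6 months postpartum, and maternal nutritional status is a key secondary outcome.

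**The concern.** WAZ is an interval score. Its zero is the reference median, and the underweight prevalences in *Study setting {9}* put the expected means well below zero. A ratio of two negative means falls below 1 when the intervention helps. It depends on how far the control mean lies from zero, and it changes sign as the means cross zero. Education and wealth subgroups can be expected to differ in control mean, so an identical benefit would be reported as different effects. An RII calculated on z-scores behaves in the same way.

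The maternal underweight subgroup raises a different issue. If mothers are classified by a value taken at 2 months postpartum or later, the package may already have moved some of them across the cut-off. Women classed as low in one arm are then not the counterparts of those classed as low in the other, and the within-subgroup contrast is no longer protected by randomisation.

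At stake is the reading of the secondary subgroup and equity results.

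**Working it through.** **1. The plan's own figure.** The protocol states 527 infants per arm per stratum for a 0.20 SD difference at 90% power and 95% confidence. The normal formula gives n = 2(1.960 + 1.282)²/0.20² = 526 after rounding up, and the noncentral t gives 527 (power 0.9004). The figure reproduces and is not disputed. It supplies the 0.20 effect and the sample size used below.

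**2. Ratio of mean WAZ under an identical benefit.** *Study setting {9}* gives 12-month underweight (WAZ below -2) as 20% in preterm and 36% in term SGA infants. Assume a normal distribution with SD 1, so mean = -2 - z(p).
- 20%: -2 + 0.842 = -1.16
- 36%: -2 + 0.358 = -1.64

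For a uniform benefit of +0.20, ratio = (m + 0.20)/m.
- m = -1.16: -0.96/-1.16 = 0.83
- m = -1.64: -1.44/-1.64 = 0.88

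Over a wider range of assumed control means:

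| Control mean | Ratio for the same +0.20 |
|---|---|
| -1.5 | 0.87 |
| -0.5 | 0.60 |
| -0.2 | 0 |
| -0.1 | -1.0 |
| +0.1 | 3.0 |

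The difference in means is 0.20 in every row. Attained weight has a true zero, so a ratio can be read there, but it still departs from *Main effects*.

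**3. RII on z-scores.** Assume means of -1.6 in the bottom and -0.6 in the top socioeconomic position.
- Before: RII = -0.6/-1.6 = 0.375; SII = -0.6 + 1.6 = 1.0
- After +0.20 for everyone: RII = -0.4/-1.4 = 0.286; SII = -0.4 + 1.4 = 1.0

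The relative index moves although nobody's relative position has changed. The absolute index does not.

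**4. Maternal MUAC subgroup.** The protocol gives no maternal MUAC distribution, so every input to this simulation is assumed: mean 25 cm, SD 2.8 cm, measurement noise SD 0.5 cm, correlation of 0.25 between baseline MUAC and infant WAZ, and a true effect of 0.20 in everyone. Mothers are grouped by MUAC below 23 cm at 2 months.

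| Assumed MUAC rise from package | Low, control v intervention | Effect, low MUAC | Effect, high MUAC |
|---|---|---|---|
| 0 cm | 24.0% v 24.1% | 0.206 | 0.200 |
| 0.2 cm | 24.1% v 21.9% | 0.184 | 0.191 |
| 0.5 cm | 24.1% v 19.0% | 0.169 | 0.182 |

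The first row is free of bias apart from simulation error. In the other two rows both subgroup effects are understated, and the false difference between subgroups is about 0.01.

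**5. What an interaction estimate could show.** With 527 analysed per arm in a stratum and a smaller-subgroup share s (assumed), SE = √[2/(527s) + 2/(527(1-s))] in SD units. The smallest interaction detectable at 90% power is (1.960 + 1.282) × SE.
- s = 0.5: SE 0.123; detectable 0.40 SD; power for a 0.20 SD interaction 37%
- s = 0.3: detectable 0.44 SD; power 32%
- s = 0.2: detectable 0.50 SD; power 25%

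**The case against.** The best defence is that the sentence on relative measures is loose and was written with the binary outcomes in mind. *Main effects* already fixes differences in means for continuous outcomes, and the protocol defines underweight, stunting and wasting as binary, where relative measures are natural. Ponderal and linear growth could mean attained weight and length, which have true zeros. That is a possible reading, and it is why the RII point is stated conditionally. It does not rescue the subgroup sentence, which is unrestricted while both primary outcomes are continuous.

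On maternal MUAC and BMI, the baseline list is introduced as non-exhaustive, and the SPIRIT figure and additional files are not shown, so an undescribed baseline measurement cannot be excluded. The article describes no measurement of maternal height either, although BMI needs one. This stands, and it makes the point conditional. Height differs in one respect: supplementation will not change it, so its timing matters less.

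Four stronger readings are tempting and are not supported:
- *That the equity analysis is relative only and untested.* The same section plans the SII, and an F-test with 95% CI for differences in the concentration index.
- *That the absence of an interaction test is itself an error.* The article is silent on it, and an analysis plan commonly supplies it.
- *That an identical effect would look several-fold larger in better-off groups.* This needs control means near zero. Means of -0.30 and -0.10 give ratios of 0.33 and -1.0, but at SD 1 they imply about 4.5% and 2.9% underweight. Nothing in the protocol places a subgroup there.
- *That maternal measurements begin 2 months after supplementation starts.* The text says 2 months postpartum and gives no date for the first maternal supplement.

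**Conclusion.** The concern holds in a limited form. As written, the subgroup rule conflicts with the main analysis and prescribes a measure that cannot be interpreted for WAZ. At the means implied by the protocol's own prevalences the distortion is modest (0.83 against 0.88 for the same benefit, assuming normality and SD 1). The fault is that the measure has no fixed meaning or direction, not that a large error has been shown. The RII criticism applies only if growth is analysed as z-scores.

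The maternal underweight subgroup rests, on the measurements described, on post-randomisation values that the package may change. Under assumed inputs the bias is small (0.17 to 0.19 against 0.20), and it disappears if MUAC is not affected. This is a matter of validity and clarity. It would be too strong to infer that the subgroup result is seriously biased.

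Both points concern secondary analyses. Neither touches the primary comparison or the sample size.

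**What to change.** Amend *Pre-specified sub-group analysis* as follows.
- For weight, WAZ and LAZ, report the difference in means within each subgroup, with the arm-by-subgroup interaction and its 95% CI. Present the interaction as an estimate, since power for a 0.20 SD interaction is at best about 37%.
- For binary outcomes, report relative risk and risk difference, as in *Main effects*.
- State the form in which growth enters the inequality analysis. Limit the RII to binary or true-zero outcomes, and rely on the already planned SII for z-scores.
- State when maternal weight, height and MUAC are taken for subgrouping. Define the MUAC/BMI subgroup from values recorded at or before randomisation. If none exist, drop that subgroup or label it post-randomisation and exploratory.

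The cost is analysis wording, with no change to conduct or sample size. The one possible loss is the maternal MUAC/BMI subgroup, if no baseline value was recorded.

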### Eligibility criteria **{10}**

#### Inclusion criteria

Preterm or term SGA infants and their mothers with ultrasound dating scan done within 20 weeks of gestation are eligible for participation.

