### Recruitment {15}

Accounting for a possible 20% loss to follow-up from enrolment to 12 months of age, we will need 650 infants per arm per stratum. We will therefore enroll a total of 2600 infants (1300 preterm and 1300 term SGA).

With 650 infants in each stratum in each arm, assuming a prevalence of underweight of 25% in the control arm at 12 months of age, we will be able to detect a 30% relative reduction in underweight, with 90% power and 95% confidence level. A narrow effect size in the hypothesis has been considered to adjust for some earlier impact of similar intervention in the study area, by our team [1]. We will also be able to detect a difference of 3 composite standard score–points (0.2 SD) in the domains of the Bayley Scales of Infant and Toddler Development, 3rd Edition (BSID-III).

Assuming 25% of babies are term SGA and 15% preterm, and 40% attrition from pregnancy identification to enrolment, we will probably need gestational age assessment through dating ultrasounds in ~13,000 pregnancies [1]. The sample size estimation for this study was conducted using *power* commands in STATA.

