**Mother**		
Health	Counselling on postnatal check-ups and family planning	
Nutrition	*6 months postpartum* Nutritional supplementation to mother in the form of healthy snacks, calcium and vitamin D, iron and folic acid supplementation, and multiple micronutrient tablets	
Psychosocial support	Promotion of positive thinking and problem-solving skills	

In the health domain, the key components are prevention, early identification, and management of infections [49]. Mothers are counselled to seek vaccination of the infants according to the national immunization schedules. They are also counselled and given demonstrations on correct handwashing practices during food preparation and feeding of the baby. Any illnesses reported by caregivers are managed at the study clinic in the collaborating hospital or any nearby health facilities [50, 51].

From enrollment to 6 months, mothers are counselled and supported to breastfeed their infants exclusively. For late preterm infants (34 to 37 weeks) who show signs of tiring quickly and suckle for less than 5 min, the mother is encouraged to give expressed breast milk feeding after each breastfeed. For infants less than 34 weeks gestation, expressed breastmilk is given following each direct feed. Mothers are taught to express, store and feed breastmilk [52, 53].

Mothers are taught to keep the baby in the skin-to-skin contact (SSC) position, i.e., upright between her breasts, and counselled to give SSC as long as possible during the day and night, in a semi-reclining or supine position, till the baby is 28 days old or wriggles out.

All infants are provided micronutrient supplementation daily as per 2022 WHO guidelines for preterm or LBW infants (iron 2–4 mg/kg/day, vitamin D 800 IU/day, and zinc 2–3 mg/kg/day) [54].

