## Statistical analysis {#20a, 20b, 20c}

### Definitions

Gestational age at birth is determined by subtracting the date of the dating ultrasound from the date of birth and then adding the gestational age assessed during that dating procedure, which follows the INTERGROWTH-21 protocol [72, 73]. Preterm births are defined as births occurring at < 37 completed weeks of gestation. Birth weight centiles are calculated using the INTERGROWTH-21 standard using weight captured within 72 h of birth and gestational age at birth [1]. SGA is defined as birth weight < 10th centile using the INTERGROWTH-21 standard [1].

Weight-for-age, length-for-age, and weight-for-length *z* scores are calculated based on weight and length measured at 12 months (± 28 days).

Proportion stunted, underweight, and wasted will be defined as having length-for-age *z* score < − 2 SD, WAZ < − 2SD, and weight-for-length *z* score < − 2SD, respectively, using WHO standards [56]. The neurodevelopmental outcome will be the composite scores of cognitive, language, motor, and socio-emotional scales and scaled scores of receptive language, expressive language, fine motor, and gross motor domains of BSID-III at 12 months of age.

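### The a priori analysis by type of preterm has no late preterm category and leaves the limits at 32 and 34 weeks undefined

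*Protocol article*

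**What the plan says.** Under Pre-specified sub-group analysis the protocol article first lists maternal and household subgroups and says of them: "Relative measures of effect within each of these sub-groups will be estimated". It then adds: "An a priori analysis will also be done for types of preterm". Two types follow, introduced as a closed list: "very (gestational age 28–32 weeks) and moderate, i.e., (gestational age 32–34 weeks) preterm". No third type is given, and no reason for stopping at 34 weeks.

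The population is defined more widely:

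- Definitions: "Preterm births are defined as births occurring at < 37 completed weeks of gestation".
- Inclusion criteria: "Preterm or term SGA infants and their mothers with ultrasound dating scan done within 20 weeks of gestation are eligible for participation". Neither these nor the exclusion criteria set a gestational-age limit within preterm.
- Recruitment {15}: "We will therefore enroll a total of 2600 infants (1300 preterm and 1300 term SGA".

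Intervention description {11a}, in the text after Table 1, separates two preterm groups at 34 weeks for feeding support. One provision begins "For late preterm infants (34 to 37 weeks) who show signs of tiring quickly"; the other reads "For infants less than 34 weeks gestation, expressed breastmilk is given following each direct feed".

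**The concern.** The article uses a late preterm group when it describes how the package is delivered, then drops that group from the analysis by preterm type. Gestational age is an obvious candidate for modifying the effect, because one component of the package is itself delivered differently on either side of 34 weeks. The one pre-specified analysis by gestational age cannot compare those two sides, since it has no category above 34 weeks.

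Two things are at stake. A late preterm estimate added once results are known would be post hoc, although it could be pre-specified now at almost no cost. And because adjoining categories share a limit, the analyst would have to decide where 32-week and 34-week infants belong, possibly with the data in hand.

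**Working it through.** **Inputs**

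- Categories: 28–32 and 32–34 weeks (Pre-specified sub-group analysis).
- Stratum: below 37 completed weeks (Definitions), no lower limit (Eligibility criteria).
- Preterm stratum 1300, 650 per arm, 20% loss to follow-up (Recruitment {15}).
- Target 0.20 SD, 90% power, 95% confidence (Sample size {14}); two-sided 5% assumed.
- Late preterm share: not in the document. Assumed range 50% to 85%.

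**Stratum size reproduced.** n per arm = 2(1.95996 + 1.28155)² / 0.20² = 2 × 10.5074 / 0.04 = 525.4, so 526. The t-test version gives 526.3, rounded up to 527, which is the stated figure. The sample size is not in question here.

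**Assignment of each completed week**

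| Completed week | Both limits included | Upper limit excluded |
|---|---|---|
| <28 | none | none |
| 28–31 | very | very |
| 32 | very and moderate | moderate |
| 33 | moderate | moderate |
| 34 | moderate | none |
| 35–36 | none | none |

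Weeks 35 and 36, and anything below 28, are in no category on either reading. Weeks 32 and 34 depend on the reading. The intervention text, with its cut at 34 weeks, points to the right-hand column, but the subgroup section does not say so.

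**Size under the assumption** (late preterm counted from 34 weeks)

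- Omitted: 1300 × 0.50 = 650, up to 1300 × 0.85 = 1105.
- Left for the two named categories: 1300 − 650 = 650, down to 1300 − 1105 = 195. These are maxima, since they include any infant below 28 weeks.
- If 34-week infants are counted as moderate, the number omitted falls by however many there are, which the document does not tell us.

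**Precision, for illustration.** Evaluable per arm = infants × 0.8 / 2. Power for 0.20 SD = Φ(0.20√(n/2) − 1.96).

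- Both named categories pooled, 50% late preterm: n = 650 × 0.8 / 2 = 260; Φ(2.280 − 1.960) = Φ(0.320), about 63%.
- Both named categories pooled, 85% late preterm: n = 195 × 0.8 / 2 = 78; Φ(1.249 − 1.960) = Φ(−0.711), about 24%.
- Omitted late preterm group, 85%: n = 1105 × 0.8 / 2 = 442; Φ(2.973 − 1.960) = Φ(1.013), about 84%. At 50% it also has n = 260 and about 63%.

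Across this range the omitted group would be estimated at least as precisely as the two named categories together.

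**The case against.** The strongest reply is that the sentence announces an analysis of two named types and does not claim to divide up the stratum. The investigators may have meant to focus on earlier births, and the whole-stratum estimate would mostly reflect late preterm infants anyway if they are the majority. That is possible, but the text neither says it nor gives a reason, and the whole-stratum estimate cannot show whether the effect differs by gestational age.

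A second reply is that shared end points are ordinary shorthand. This has force. A reader might infer that 32-week infants will be counted twice and also that every infant from 34 weeks is excluded. Those two inferences need opposite readings of the same notation, as the table shows, so they cannot both be asserted. What stands is that the limits are not fixed and that 35 to <37 weeks is missing on either reading.

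A reader might also infer that WAZ will be analysed as a ratio, because relative measures are promised within subgroups. That sentence comes before the preterm one and refers to the maternal and household subgroups. The Main effects section already fixes differences in means for continuous outcomes.

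Nor is the absence of an interaction test an error in this document: it may be in the analysis plan, which is not shown.

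Finally, the exclusion of babies or mothers hospitalised for more than 14 days after delivery may leave few infants below 28 weeks, so that gap could be nearly empty.

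**Conclusion.** The point holds as a defect in stated text. The a priori categories omit at least 35 to <37 weeks, or 34 to <37 weeks on the cut used in the intervention text. They also omit any infant below 28 weeks, and week 32 has no unique assignment. Nothing elsewhere in the article repairs this.

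The number affected is unknown. The figure of 650 to 1105 out of 1300 rests wholly on the assumed 50% to 85% share and on counting late preterm from 34 weeks. The gap itself follows from the stated limits and needs no assumption about that share.

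A reader might infer that the preterm efficacy result is compromised. The documents do not support that: the primary comparison uses the whole stratum, and its sample size and type I error are untouched. This is a correction worth making to a secondary analysis.

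**What to change.** Before unblinding, restate the categories in weeks and days so that they are exclusive and cover the stratum: <32+0, 32+0 to 33+6, and 34+0 to 36+6. If leaving out late preterm infants is intended, say so and give the reason.

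Estimate the mean difference in attained weight and in WAZ within each category from one Gaussian identity-link model, as already named under Main effects, with an arm-by-category interaction. Report the interaction estimates with their 95% confidence intervals beside the within-category differences.

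The cost is a sentence or two in the protocol and the analysis plan. Gestational age at birth is already derived from the dating scan and the date of birth, so no new data are needed. The downside is one more subgroup estimate and low precision in the smaller categories, which the report should state.
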